#### **14.2.2 Acceptability**

At the Week 12 and Week 16 visit, volunteers will be asked about their willingness to use the drug regimen in the future if it is proven to be effective. The most recent response will be used for analysis. Volunteers who drop-out of the study prior to Week 12 will be assumed to be not willing to use the drug regimen. Volunteers who become HIV infected will be excluded. The proportion of volunteers in the daily FTC/TDF group who express their willingness will be calculated along with the exact, two-sided, 95% confidence interval for the true proportion. Likewise, the proportion of volunteers in the intermittent truvada group will be calculated. The same analyses will be performed for the HIV-infected partners' opinion on the acceptability of their partner using the drug regimen in the future if it is proven to be effective.

#### **14.2.3 Days per week on which study treatment is used**

For each study month, the average number of days per week on which study treatment was used will be calculated. The proportion of volunteers using study treatment 5 or more days a week will be calculated. The frequency of study treatment use on each day of the week will be calculated.

#### **14.2.4 Adherence**

The mean, median and range of adherence to PrEP will be determined using MEMS data for volunteers. Previous work has shown that the accuracy of MEMS assessment can be improved with a 3-day structured self-report of the number of extra cap openings and the number of times multiple doses are taken out of the bottle [119]. The *adjusted MEMS adherence* is calculated by the interview adjusted number of bottle openings/number of doses prescribed over the prior three days. The *unadjusted MEMS* measure is the number of electronically recorded bottle openings divided by the number of expected doses based on IVR sexual activity data, since the last interview[48]. MEMS adherence will be classified by the schema proposed by Vrijens where adherence is organized in terms of persistence and execution [161,162]. Persistence is time to treatment discontinuation. Treatment discontinuation will be defined as the first day of 30 consecutive days without a MEMS cap event. Treatment execution is defined as the number of MEMS caps events divided by the number of expected doses prior to treatment discontinuation. We also will use MEMS to characterize treatment interruptions and whether patterns of adherence are temporally related to sexual behavior. These approaches have been successfully piloted in Uganda [77,94].

For volunteers assigned to intermittent regimens, a combination of MEMS and IVR/SMS data will be used. Each day will be classified as an adherent or nonadherent day. Adherent days will be defined as: any day on which sexual activity was reported and a MEMS event occurred, any Monday or Friday on which a MEMS event occurred, and any other day of the week on which neither sexual activity nor a MEMS event occurred. Adherence will be calculated as the number of adherent days since the last visit divided by the number of days since the last visit.

We will examine the degree of correspondence between MEMS and 30 day recall data using a linear model, taking repeated measures into account, to compare predicted adherence from MEMS and IVR/SMS with 30 day recall data. Similarly adherence from MEMS will be compared with plasma and intracellular drug levels for correspondence. We will determine if PrEP adherence declines over time by comparing median adherence each month using a linear model, testing for a non-zero slope and proportion >90% adherent using logistic regression. Finally we will describe time to PrEP discontinuation (or non-persistence), defined by >30 days without a MEMS event, with Kaplan-Meier methods. Volunteers who discontinued study treatment due to intolerance, toxicity, or pregnancy will be censored at the time of treatment discontinuation.

With 24 volunteers per treatment group, a two-sided, 0.05 level binomial test of 75% adherence will have only 29% power to detect a true adherence rate of 90%. Power increases to 66% if the true adherence rate is 95%.

If we combine the intermittent FTC/TDF and intermittent placebo groups (n=36), then a two-sided, 0.05 level binomial test of 75% adherence will have 51% power to detect a true adherence rate of 90%. Power increases to 90% if the true adherence rate is 95%. Likewise, if we combine the daily FTC/TDF and the daily placebo groups (n=36), we will have reasonable power to detect high rates of adherence.

The relationship between adherence and intracellular drug level will be evaluated in the volunteers assigned to active regimens FTC/TDF. Determining the relationship between adherence and intracellular drug levels may provide adherence estimates for future studies which do not include detailed objective adherence measures. The correlation between mean adherence execution over the prior month and intracellular drug level will be tested using Pearson's correlation coefficient. Mean drug levels in individuals with  $\geq 90\%$  adherence will be compared with those with <90% adherence using a student's T test.

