Limitations of MEMS are that it records bottle opening and not actual medication dosing. In addition, patients may take out more than one dose at a time, or “pocket doses.” At other times, patients may open the pill bottle without taking the medication, called “curiosity events” [95,96]. These behaviors lead to an underestimation or overestimation of actual adherence, respectively. The MEMS-based adherence rate can be adjusted to account for pocket doses and curiosity event, if the individual records and conveys such information to the study staff. MEMS also precludes the use of medication pill-box organizers, which have been associated with modest (4%) but highly cost-effective increases in adherence in observational studies [97,98].

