##### *Intracellular drug concentrations:*

- The mean intracellular drug concentration for each group assigned to FTC/TDF

*Adherence:*

- The proportion of volunteers, who by MEMS data, took at least 80% of expected doses of the investigational product
- The proportion of volunteers assigned to FTC/TDF who have detectable drug plasma levels within 48 hours of reported use
- The relationship between intracellular drug levels and adherence in volunteers assigned to FTC/TDF

*Behavioural:*

- Reported number of steady and casual sex partners
- Frequency of unprotected vaginal intercourse
- Substance use prior to or during sex

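### Section 14.2.4 counts raw bottle openings against expected doses, so extra openings can offset missed doses, and no passage says which of its adherence measures feeds the 80% endpoint

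*Protocol*

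**What the plan says.** The primary adherence endpoint in section 5.1.1 is the proportion of volunteers who, by MEMS, "took at least 80% of expected doses of the investigational product". Section 14.2.4 gives four calculations that could bear on it.

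- Unadjusted MEMS: the "number of electronically recorded bottle openings divided by the number of expected doses". Expected doses come from the phone reports of sex, and the count runs from the previous interview.
- Execution: "Treatment execution is defined as the number of MEMS caps events divided by the number of expected doses prior to treatment discontinuation".
- Adjusted MEMS: "calculated by the interview adjusted number of bottle openings/number of doses prescribed over the prior three days".
- For the intermittent arms only, a day-level rule. A day counts as adherent if sex was reported and a MEMS event occurred, if it is a Monday or Friday with an event, or if it is "any other day of the week on which neither sexual activity nor a MEMS event occurred". The score is the adherent share of all days between visits.

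Table 1 in section 5.2 limits dosing to one tablet a day in both regimens. Section 3.3.3.1 acknowledges that "patients may open the pill bottle without taking the medication", which overstates adherence, and that volunteers may remove several doses at one opening, which understates it. The synopsis calls for percent adherence over the whole study interval and derives the intermittent group's expected doses from daily reports of sexual activity.

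**The concern.** The endpoint asks what share of expected doses was taken. The first two formulas instead divide all openings by expected doses. A second opening on Tuesday makes up for a missed Wednesday, and in the intermittent arms an opening on a Tuesday without sex makes up for a missed Friday. A volunteer who misses more than a fifth of expected doses can be classed as adherent.

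In the intermittent arms the same off-schedule opening raises the ratio and lowers the day-level score, so classification at 80% depends on the formula chosen. Comparing adherence between regimens is a primary objective (section 4.1). If the daily arms were scored by the ratio and the intermittent arms by the day rule, that comparison would set two different quantities against each other.

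Section 13.3 requires the analysis plan to be agreed only before unblinding. The regimen is open and MEMS data are uploaded at visits, so adherence by regimen could be seen before the measure is chosen.

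**Working it through.** **The plan's own figures.** Section 14.2.4 gives the power of a two-sided 0.05 binomial test against 75% adherence. With exact equal tails the upper rejection bounds are at least 23 of 24 and at least 33 of 36.

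| n | True rate | Stated power | Recomputed |
|---|---|---|---|
| 24 | 90% | 29% | 29.2% |
| 24 | 95% | 66% | 66.1% |
| 36 | 90% | 51% | 50.9% |
| 36 | 95% | 90% | 89.6% |

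These figures are right and not in dispute. They show that reclassifying a single volunteer, from 32 to 33 of 36, can change the test result.

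**Which measures fit the daily arms.** The day-level rule is restricted to the intermittent regimens. The adjusted ratio covers three days before an interview and cannot give adherence over the study interval. That leaves the unadjusted ratio and execution, both uncapped and unmatched.

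**Daily record.** Sixteen weeks is 112 days, so 112 doses are expected. Suppose 80 days are dosed and there are 12 extra openings.

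- Matched: 80/112 = 71.4%.
- Ratio: (80 + 12)/112 = 92/112 = 82.1%.

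**Intermittent records.** There are 16 × 2 = 32 Monday and Friday doses. Assume 16 sex days on other weekdays, so 48 doses are expected and 112 − 48 = 64 days have none.

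- Record (b): all 32 scheduled doses, no post-sex dose, 10 openings on days with no expected dose.
  - Ratio: (32 + 10)/48 = 42/48 = 87.5%.
  - Day rule: (32 + 64 − 10)/112 = 86/112 = 76.8%.
  - Matched: 32/48 = 66.7%.
- Record (c): one opening every day.
  - Ratio: 112/48 = 233%.
  - Day rule: 48/112 = 42.9%.
  - Matched: 48/48 = 100%.

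One extra opening is worth 1/112 = 0.9 points in the daily regimen and 1/48 = 2.1 points in the intermittent example.

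**The day rule on its own.** A volunteer who reports no sex and never opens the bottle scores 5/7 = 71.4%.

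**Illustrative simulation.** The protocol gives no rate for extra openings, so every input is an assumption: 112 days, 70% of expected doses taken, sex on 2/7 of days other than Monday and Friday. Extra openings occur with the stated probability per day in the daily regimen, and per day without an expected dose in the intermittent regimen. Entries are the share of volunteers classed at or above 80%.

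| Extra-opening probability | Daily, ratio | Intermittent, ratio | Intermittent, day rule |
|---|---|---|---|
| 0 | 0.9% | 5.4% | 94.9% |
| 0.05 | 15.2% | 25.5% | 79.5% |
| 0.10 | 50.7% | 53.2% | 54.1% |
| 0.15 | 82.2% | 76.3% | 28.6% |

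Matched scoring gives 0.9% (daily) and about 5.4% (intermittent) throughout. In the first row the two regimens have the same 70% dose-taking and no extra openings. Even so, scoring daily by the ratio and intermittent by the day rule would report 0.9% against 94.9%.

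**The case against.** The protocol does not ignore extra openings. The adjusted ratio corrects for them and the day rule penalises them. The synopsis reports intermittent adherence separately for scheduled and sex-day doses, which would show record (b) as full on one and nil on the other. Section 14.2.3 reports days of use per week, which would expose record (c). Pill counts, self-report and drug levels offer further checks. Capping and matching could also be left to an analysis plan not shown here, and this is a small pilot with acknowledged low power.

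Much of this stands as mitigation, but it does not repair the printed formulas. The adjusted ratio covers three days and depends on self-report. The day rule does not apply to the daily arms and does not divide by expected doses. An analysis plan that capped or matched events would have to depart from the protocol's definitions.

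Two stronger readings are tempting.

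- A reader might infer that the plan inflates the primary 80% endpoint. The endpoint wording fits the ratio, but no passage ties the two together. Under the day rule, records (b) and (c) both fall below 80%. Doses removed in advance bias the ratio downward, so even its net error is not certainly upward.
- A reader might infer that inflation is greater in the intermittent arms, biasing the comparison in a known direction. One opening weighs more there, but the rise in the share classed adherent is about 14 points daily against 20 intermittent at 0.05, 50 against 48 at 0.10, and 81 against 71 at 0.15. The order reverses, so no direction is established.

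A fair objection also applies to the remedy. A post-sex dose may fall after midnight, and section 9.5 records sex as having occurred the previous day. Strict calendar-day matching would score such a dose as both missed and extra.

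**Conclusion.** The point holds as a defect in stated formulas together with an unassigned endpoint. Unadjusted MEMS and execution let extra openings offset missed doses and can exceed 100%. In the daily arms nothing else printed can supply the 80% endpoint. In the intermittent arms the ratio and the day rule move in opposite directions for an off-schedule opening, and record (b) changes class between them.

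The record arithmetic rests only on the printed rules and the example records. The simulated shares rest on assumed dosing, sex-day and opening rates and show only what is possible. Neither establishes the net direction or size of the bias in this trial, because extra-opening and advance-removal rates are unknown.

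**What to change.** In section 14.2.4:

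- Name one measure for the 80% endpoint in all arms: expected doses with at least one MEMS event, divided by expected doses. Credit at most one event per expected dose.
- State an event window, so that a late or post-sex dose recorded after midnight is credited to the dose it belongs to.
- For execution as used in the correlation with intracellular drug level, which is itself a primary adherence endpoint, cap at one event per dosing day but keep off-schedule events. Tablets taken off schedule also raise drug levels, so matching would discard relevant exposure.
- Report extra and off-schedule openings separately, and keep the raw ratio and the day-level rule as sensitivity analyses.

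The cost is revised wording and modest programming on time-stamped data already being collected. Reported adherence will probably be slightly lower than under the raw ratio.

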#### **6.5 Week 16 /Early Termination Visit for HIV-uninfected volunteers**

Assessments and procedures will be performed according to the Schedule of Procedures (Appendix A1).

Research centre personnel will:

- Review interim medical history and use of concomitant medications
- Perform a general physical examination including weight, vital signs (pulse, respiratory rate, blood pressure and temperature), examination of skin, respiratory, cardiovascular and abdominal systems, and external genital exam.
- Collect blood and specimens for tests as specified in the Schedule of Procedures (Appendix A1).
- Perform a pregnancy test for all female volunteers.
- Conduct HIV pre-test counselling or provide post-test counselling if the results of a prior HIV test are being provided to the volunteer.
- Collect data on Adverse Events and Serious Adverse Events
- Upload MEMS data
- Collect self-report information on adherence, sexual risk behaviour, investigational product acceptability and medication sharing (i.e., follow back interview)
- Collect unused pills and MEMS TrackCap

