## **6.7 Final Visit**

After stopping study drug at week 16 (see section 6.5), volunteers will have one additional follow-up visit at week 24, to assess for undetected HIV infection and immune responses once off study drug.

Research centre personnel will:

- Conduct HIV pre-test counselling or provide post-test counselling if the results of a prior HIV test are being provided to the volunteer.
- Collect blood and specimens for tests as specified in the Schedule of Procedures (Appendix A).
- Conduct HIV post-test counselling
- Provide HIV risk reduction counselling

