### 9.4. Adherence Assessments

Adherence to and dosing of investigational product will be assessed through MEMS data, follow-back interview and plasma/intracellular drug levels at the time points indicated in Appendix A1.

*MEMS electronic medication-monitoring pill bottle caps.* Daily medication adherence data will be collected using the AARDEX Medication Event Monitoring System (slightly larger than a standard pharmacy-sized bottle cap with an electronic chip that clocks bottle openings in a 24-hour period). This measure provides complete information on patterns of adherence, including treatment interruptions. Each volunteer will be assigned a MEMS TrackCap to be used on his or her study drug pill bottles. MEMS data for all volunteers regardless of assignment group will be uploaded from the device at monthly visits as indicated in Appendix A1.

*Self-reported adherence.* At timepoints indicated in the Schedule of Procedures (Appendix A1) self-reported adherence to PrEP will be collected using a follow-back interview which is a structured self-report of number of doses missed. A 30 day self-report was shown to be closely associated with MEMS adherence in Uganda [77,110].

*Plasma drug levels.* Plasma from all volunteers will be stored at multiple visits as indicated in Appendix A1 for retrospective assessment of drug plasma levels in those volunteers assigned to FTC/TDF. The plasma half-life of tenofovir after a single oral dose is approximately 17 hours, but drug remains detectable (>10ng/mL) out to 48 hours [43]. At the end of the study after treatment assignment has been unblinded, samples will be selected from up to 4 visits when the volunteer's MEMS data indicate dosing with FTC/TDF within 48 hours of the visit and tested for plasma drug levels.

Two additional adherence measurements will be explored. Intracellular drug levels will be measured in volunteers assigned to FTC/TDF. PBMCs will be collected from all volunteers at the time points indicated in Appendix A1. After

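### The 30-day gap rule cannot register a stop in the last 29 to 30 days before the cap is returned, so persistence read near Week 16 is too high and execution depends on the date of stopping

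*Protocol*

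**What the plan says.** Protocol section 14.2.4 splits MEMS adherence into persistence and execution. On the first it says "Persistence is time to treatment discontinuation", and it fixes the event: "Treatment discontinuation will be defined as the first day of 30 consecutive days without a MEMS cap event". Execution is cap events divided by the doses expected before that discontinuation date. Later in the same section the threshold changes: "Finally we will describe time to PrEP discontinuation (or non-persistence), defined by >30 days without a MEMS event, with Kaplan-Meier methods". The only censoring stated there is for product-related or pregnancy stops: "Volunteers who discontinued study treatment due to intolerance, toxicity, or pregnancy will be censored at the time of treatment discontinuation".

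The observation period is fixed elsewhere in the protocol. Section 9.4 says MEMS data "will be uploaded from the device at monthly visits as indicated in Appendix A1", and Appendix A1 marks uploads at Weeks 4, 8, 12 and 16 (or early termination). The Week 16 window is -7/+2 days. At that visit section 6.5 has staff "Collect unused pills and MEMS TrackCap", and section 6.7 confirms the end of dosing: "After stopping study drug at week 16 (see section 6.5), volunteers will have one additional follow-up visit at week 24".

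**The concern.** A volunteer becomes an event only after 30 or more silent days have been recorded. Recording ends when the cap is handed in. A stop that begins too close to that visit cannot reach the threshold, so it is never classed as discontinuation, however long the volunteer would have stayed off the product. The same applies to an early terminator who returns the cap within about a month of the last dose.

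Two things are at stake. First, a persistence figure taken at or near Week 16 counts late stoppers as persistent. Second, the discontinuation date also sets the execution denominator. Silent days after an early stop drop out of execution, while silent days after a late stop stay in it. The persistence and execution scheme is meant to keep these two behaviours apart, and section 14.2.4 then correlates execution over the prior month with intracellular drug level. The relationship between drug level and adherence is a listed primary endpoint in section 5.1.1.

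**Working it through.** The plan gives no persistence figure, so there is none to reproduce. Days are numbered so that Week 16 is day 16 × 7 = 112.

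**Step 1: the last day on which a stop can be registered.** Latest first silent day = last upload day − gap length + 1. The gap length is 30 days under the definition and 31 under the Kaplan-Meier sentence (more than 30).

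| Last upload | 30-day gap | More than 30 days |
|---|---|---|
| Day 105 (−7) | day 76; 29 blind days (27.6%) | day 75; 30 blind days (28.6%) |
| Day 112 | day 83; 29 blind days (25.9%) | day 82; 30 blind days (26.8%) |
| Day 114 (+2) | day 85; 29 blind days (25.4%) | day 84; 30 blind days (26.3%) |

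After the day shown, no new event is possible and the curve is flat whatever volunteers do.

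**Step 2: size of the error if the curve is read at Week 16.** The documents give neither the rate nor the timing of stopping. Assume a constant hazard, a day-112 upload, a 30-day gap and true Week 16 persistence S of 70% to 95%. The curve at day 112 then equals the true value at day 83, which is S^(83/112). A simulation of 200,000 volunteers per row gives:

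| True S(112) | S^(83/112) | Simulated Kaplan-Meier at day 112 | Overstatement (simulated) | Stoppers missed |
|---|---|---|---|---|
| 0.95 | 0.963 | 0.962 | 1.2 points | 26% |
| 0.90 | 0.925 | 0.924 | 2.4 points | 25% |
| 0.80 | 0.848 | 0.847 | 4.7 points | 24% |
| 0.70 | 0.768 | 0.769 | 6.9 points | 23% |

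Formula and simulation agree to within 0.2 points. Censoring unflagged stoppers at their last cap event instead of day 112 gives the same values. With 36 volunteers per regimen and S = 0.80, 36 × 0.20 = 7.2 stops are expected and 36 × (1 − 0.8476) = 5.5 are counted.

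**Step 3: the curve before the blind period.** Cut at day 83, the simulated curve gives 0.962, 0.924, 0.847 and 0.769, against true day-83 values of 0.963, 0.925, 0.848 and 0.768. There is no error from this mechanism up to that day.

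**Step 4: execution.** Take two volunteers on the daily regimen who dose perfectly until they stop, with upload on day 112.

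- Silent from day 80: 112 − 80 + 1 = 33 silent days, so discontinued on day 80. Execution = 79/79 = 100%.
- Silent from day 90: 112 − 90 + 1 = 23 silent days, so not discontinued. Execution = 89/112 = 79%.

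For the correlation at Week 16, take days 85 to 112 (28 days) as the prior month. The day-80 stopper has no expected doses before discontinuation in that month, so execution is undefined. The day-90 stopper has 5/28 = 18%.

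**Step 5: measures that do not use the rule.** Overall adherence is 79/112 = 71% for the day-80 stopper and 89/112 = 79.5% for the day-90 stopper. Both fail the 80% MEMS endpoint.

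**The case against.** The strongest reply is that nobody has promised a Week 16 persistence figure. The protocol says only that time to discontinuation will be described. How far the curve is read, and how open gaps are handled, is ordinary content for a statistical analysis plan, which is not shown. That stands in part: the missing reading horizon is not itself the fault. The point rests on what the protocol does fix, namely the event rule, the estimator, the execution denominator and two thresholds that cannot both be followed.

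A reader might infer that persistence is overstated throughout. The documents do not support that: for volunteers who keep the cap to Week 16, the curve is unaffected by this mechanism up to about day 82 or 83. A reader might also infer that late drop-off goes unseen, or that the primary adherence endpoint is biased. Neither follows. Late stops lower overall and monthly adherence and the days of use per week, and they count against the 80% MEMS endpoint. The plan also tests for decline over time. Persistence is descriptive and is not a listed endpoint.

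Two further points stand. The rule counts someone who resumes after a 30-day gap as discontinued, which pulls persistence the other way; the documents do not say how common that would be. And at 80% true persistence with 36 volunteers, one standard error is √(0.8 × 0.2/36) = 6.7 points, more than the 4.7-point error. Small size is a reason for modest priority. It does not remove an error of known direction that wording alone can avoid, and it does not answer the execution problem.

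**Conclusion.** The point holds within limits. A stop that begins in the last 29 to 30 days before the final upload cannot be an event. For a day-112 upload that means after day 83 or day 82 depending on which threshold applies, and across the visit window the cut-off runs from day 75 to day 85. Between 25% and 29% of the dosing days are blind in this sense. Persistence read at or near Week 16 is overstated through this mechanism by about 1 to 7 points for true persistence of 95% to 70%. That range rests on an assumed constant hazard, a 30-day gap and everyone keeping the cap to day 112. More stopping late in the dosing period would make the error larger, and more stopping early would make it smaller.

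The execution effect needs no such assumption. It follows from the definition and reaches the planned correlation with drug level. The conflict between 30 and more than 30 days shifts the cut-off by one day only, but it should be settled because both sentences define the same event.

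**What to change.** In section 14.2.4, and carried into the statistical analysis plan:

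1. Use one gap threshold in both places.
2. Censor and report Kaplan-Meier persistence only to each volunteer's last upload minus the gap length (by day count, last upload day − gap + 1), and state that horizon, about 12 weeks.
3. Report by regimen the number of volunteers with a silent run still open at the last upload, with early terminators shown separately. Item 2 does not recover their stops.
4. Add a sensitivity analysis that dates discontinuation from the last MEMS event for open runs, and apply the same cut to execution. The day-90 stopper would then score 89/89 = 100%, the same as the day-80 stopper.

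Item 4 needs a stated minimum length for an open run. The documents give no basis for a particular value. It must exceed the gaps that full adherence allows: on the intermittent regimen, Tuesday to Thursday can be three silent days with no dose missed.

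The cost is wording only, with no new data or visits. The downside is that the main persistence result covers about 12 weeks instead of 16, which is as far as this definition can be observed.
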